## Abstract

**Background:**

Unhealthy dietary and physical activity (PA) patterns are highly prevalent in most Western countries, especially among lower-educated and ethnic minority groups. Therefore, interventions to promote healthy eating and physical activity that can reach large numbers of lower-educated people are needed. When developing interventions, the ethnic diversity of the lower-educated population may be taken into account to make intervention material more appealing to the target group. This article describes the development and evaluation of two computer-tailored nutrition and physical activity interventions for lower-educated Dutch, Turkish and Moroccan women. One version is tailored to sociocognitive variables (traditional tailoring), while the other is additionally tailored to ethnic identity (EI-tailoring).

**Method:**

Using intervention mapping, two evidence- and theory-based interventions were developed. In the traditional tailoring intervention, messages are tailored to health behavior, awareness of own behavior, attitude and self-efficacy. The behavior change techniques used to address these factors are: descriptive and evaluative feedback, arguments, modeling, goal setting, planning, barrier identification and advice on how to deal with barriers, stimulating resistance to social pressure, mobilization of social support (nontailored), active learning (nontailored) and iterative feedback. In the EI-tailoring intervention, the material is additionally tailored to ethnic identity (EI). This means that recipients who feel strongly attached to their ethnic background receive different intervention material than recipients with a weak attachment to their background. This includes, for instance, the use of more traditional colors, role models that match with their origin and advice messages that refer to their ethnicity of origin.

**Discussion:**

Developing an intervention that matches the needs of this specific target population was challenging due to the little evidence regarding the determinants of their health behavior, as well as the behavioral change techniques that have not been tested among Turkish and Moroccan women in the Netherlands before. Based on previous research among this and other target populations we hypothesize, however, that the determinants and strategies we use will be suitable. A randomized controlled trial will show whether the interventions are effective among our specific target group and whether EI-tailoring is beneficial.

**Trial registration:**

Dutch Trial Registry NTR4506, registration date: 1^st^ may 2014

## Background

Unhealthy dietary and physical activity (PA) patterns are highly prevalent in most Western countries [1–3] and even more so among lower-educated and ethnic minority groups [4–10]. More specifically, low fruit and vegetable intake, high consumption of energy-dense products and high percentages of people not meeting the PA norms have been reported for Western populations [2, 10–13]. Unhealthy dietary and PA behavior have been associated with negative health outcomes, such as type 2 diabetes, cancer and cardiovascular diseases [14, 15]. Lower-educated and ethnic minority groups are at higher risk of these health problems [4, 16–18]. It is, therefore, important to improve dietary and PA behaviors among lower-educated and ethnic minority groups in particular. Moreover, since the problem occurs on such a large scale, interventions are needed that can reach large numbers of people.

In the Netherlands, only 3–14 % of the general population meet the norm for vegetable consumption, and only 3–26 % consume a sufficient amount of fruit [19]. The Health Council of the Netherlands recommends eating at least 200 grams of vegetables and 200 grams of fruit every day [20]. The Netherlands Nutrition Center (Stichting Voedingscentrum Nederland) even recommends to eat 250 grams of vegetables or more [21]. The results of the most recent Dutch National Food Consumption Survey [19] showed that 25 % of adult women consume 2200 kilo-calories per day or more. In-between meal snacks, such as sugar, confectionery and cake, accounted for as much as 21 % of the daily energy intake [19]. Studies among populations with a low socioeconomic status and a lower education have shown that a low fruit and vegetable consumption is even more common in these groups [4–6], and that their snack consumption is higher [22].

In the Netherlands there is a variety of ethnic minorities, with Turks and Moroccans being among the largest groups [23]. Studies among ethnic minority groups in general [9], and Turkish and Moroccan groups in particular [24, 25], have shown that high percentages of the adults do not meet the norm for fruit and vegetable consumption. The limited available evidence on the snack consumption of Turkish and Moroccan groups in the Netherlands shows that Turkish and Moroccan women snack a lot in between meals [25, 26]. In-between meal snacks comprise 28 % of the total daily energy intake of Turkish participants, and 22 % of that of the Moroccan participants [25].

The percentage of people in the general Dutch population meeting the norm for moderate PA has been relatively constant for a number of years at around 59 %, with working, transport and household activities being the main contributors [7]. It is recommended to be moderately physically active (e.g. cycling, walking) for 30 minutes a day, on at least five days per week [7]. Lower-educated people are even less physically active than higher educated populations [27, 28]. Furthermore, research shows that only 25 % of the Moroccan and 34 % of the Turkish people living in the Netherlands meet the norm for moderate PA [7]. Recent research shows that among Turkish and Moroccan women, only 39 % meet the Dutch norm for PA [29].

To improve the dietary intake and PA levels of lower-educated and ethnic minority groups a project was initiated aimed at developing and evaluating an intervention for these specific groups. We chose to include Turkish and Moroccan people in our target population (besides people of Dutch origin), since these are among the largest immigrant groups in the Netherlands. We furthermore chose to focus on women, as a needs assessment among Dutch, Turkish and Moroccan men and women revealed that it is mainly the women that prepare the meals for the family [30]. On consulting other studies we found that the Turkish and Moroccan target populations consider cooking to be the task of women [26, 31]. As a result, we felt that focusing on women may be the most efficient approach for our intervention. Therefore, the intervention described in this paper focuses on lower-educated women of Dutch, Turkish and Moroccan origin. We aimed to develop an intervention that can reach large numbers of people, as interventions for this specific target population that have a high reach and can be implemented on a large scale are rare in the Netherlands.

An effective intervention technique that can reach large numbers of people with personally relevant information is computer tailoring [32]. In computer-tailored interventions individualized feedback and advice can be provided, which is thought to be necessary and very effective in changing complex health-related behaviors such as diet and PA. Relevant information on individual characteristics, behaviors and beliefs is first assessed and subsequently feedback and advice are provided that match the personal circumstances, behaviors and beliefs of each individual [33]. This technique has been shown to be effective among many target groups and a variety of health behaviors, including dietary and PA behavior [34–37]. There is also evidence that computer tailoring interventions can be effective for lower-educated people [38–40].

Hawkins et al. [41] argue that messages are likely to be perceived as more relevant when presented in a context that is significant to the individual, such as the cultural or demographic context, identity, ethnicity or personal interest. Consequently, by taking relevant contextual factors into account, tailoring messages may further increase the probability that the information provided is attended to and processed by groups with a specific contextual background. In other words, contextualizing intervention materials may enhance the chance of processing information centrally, as suggested by Hawkins et al. [41].

Improving attention may, in particular, be important for lower-educated and ethnic minority groups. We applied ethnic identity tailoring (EI-tailoring) to contextualize our intervention material to make it more attractive to the various sub-groups within our target population. Ethnic identity (EI) is the degree to which a person identifies with a particular ethnic group [42]. U.S. studies among African American populations have demonstrated that taking the EI or the cultural background into account when promoting a healthy lifestyle can improve the effectiveness and/or the attractiveness of health-promoting interventions [42, 43]. We used EI as a concept to contextualize our intervention materials.

The aim of this paper is to describe the systematic development of the two versions of a computer-tailored intervention aimed at promoting a healthy diet and a sufficient amount of PA among lower-educated Dutch, Turkish and Moroccan adult women living in the Netherlands.

## Method

We used the intervention mapping (IM) protocol to develop a computer-tailored intervention, as it helps to structurally develop a theory- and evidence-based intervention. IM follows six steps that are described by Bartholomew et al. [44]: 1) conduct a needs assessment, 2) create matrices of change objectives, 3) select theory-based intervention methods and practical applications, 4) develop an intervention program, 5) plan for the adoption, implementation and sustainability of the program and 6) plan the evaluation of the intervention.

### Creating the base of the intervention

Developing an intervention starts with a thorough assessment of the needs within a target group. This needs assessment results in a definition of the behaviors that should be addressed in order to improve the health of the target population, as well as a definition of specific sub-behaviors related to the behavior and their determinants. These (sub-)behaviors and their determinants create the base for an intervention. The needs assessment, which is briefly summarized in the introduction section, led us to focus on four behaviors that we aim to address with our intervention: fruit consumption, vegetable consumption, snack consumption and physical activity. Therefore, the aim of the interventions described in this paper is to improve these behaviors among the target group.

The follow-up brochure contains advice about both be-Self-regulation theories were used to formulate *performance objectives* indicating which specific sub-behaviors people should master to be able to successfully change the target behaviors. Self-regulation theories [45] state that behavior change emerges through a process of two phases. The process begins with a *pre-intentional*, *motivational phase* that includes problem identification, goal selection and goal setting. The next step involves the *post-intentional*, *volitional phase*, encompassing the translation of the goal into action by making a plan and considering solutions for how to deal with difficult situations. Additionally, the behavior must be evaluated and monitored in this phase to facilitate maintenance of the change over time [45]. The performance objectives were formulated in line with these self-regulation phases (see Table 1).

**Table 1 Tab1:** Performance objectives, represented by each phase of the self-regulation process

Motivational phase
After exposure to the intervention…
PO 1: Individuals from the target group decide to eat more fruit, more vegetables, or fewer high-energy snacks, or to engage in more PA.
PO 2: Individuals set a specific, relevant, appropriate and feasible goal to eat more fruit, more vegetable, or fewer high-energy snacks, or to engage in more PA.
Volitional phase
After exposure to the intervention…
PO 3: Individuals think of strategies that may help them eat more fruit, more vegetables, or fewer high-energy snacks, or to engage in more PA.
PO 4: Individuals make a plan specifying when, where and how to eat more fruit, more vegetables, or fewer high-energy snacks, or to engage in more PA.
PO 5: Individuals eat more fruit, more vegetables, or fewer high-energy snacks, or engage in more PA.
PO 6: Individuals evaluate if they managed to eat more fruit, more vegetables, or fewer high-energy snacks, or engage in more PA.
PO 7: If the goals have not been reached, individuals adjust their goal.

*PO* performance objective, *PA* physical activity

Determinants that may lead to the achievement of the performance objectives were derived from the literature. Determinants for behavioral change have been widely studied and suggested by theories such as self-regulation theories and the theory of planned behavior (TPB). Factors associated with diet and PA which are frequently described in the scientific literature include *awareness of one’s own risk behavior*, *knowledge*, *attitude*, *self-efficacy*, *social influences*, *intention*, *reevaluation of own behavior*, *goal setting* and *action planning* [45–51]. Focus group interviews among the target group showed that these determinants are important factors that may hinder or facilitate the behaviors in question. Furthermore, specific practical barriers and beliefs related to these determinants arose from the interviews, which will be addressed in our interventions. For instance, taste and health benefits were mentioned as attitude beliefs regarding healthy eating and PA. Barriers to eating healthily or engaging in PA included a lack of time and being too tired. For the Turkish and Moroccan participants, hospitality and religious factors were particularly mentioned as barriers to eating healthily or exercising (e.g. not being able to refuse food on social occasions, and men and women cannot exercise in the same location) [30]. In line with the IM procedure, the performance objectives and determinants were combined in a matrix. *Change objectives* for each performance objective-determinant combination were formulated to clarify what participants should learn as a result of the intervention, e.g.: *after having received the intervention, individuals state that eating more fruit is good*.

### Configuring intervention content and material

After having defined the behaviors and determinants to address, the intervention content was designed and two versions of a computer tailoring intervention were developed: one that includes tailoring to sociocognitive variables (traditional tailoring intervention) and one that additionally includes tailoring to the EI to contextualize the intervention material (EI-tailoring intervention).

The traditional tailoring intervention consists of written feedback messages tailored to the recipients’ behavior and the above described determinants of the behavior. The feedback messages are delivered in a sequence of three printed brochures (see Fig. 1 for an example of a cover page of the traditional tailoring intervention). The first two brochures contain advice about two of the following behaviors: 1) fruit consumption, 2) vegetable consumption, 3) snack consumption, 4) PA. The recipient receives feedback on only two of the four behaviors, as addressing too many behaviors at a time may lead to ego depletion and because self-regulation might be a limited source [52, 53]. The third brochure is a follow-up brochure containing follow-up feedback on the behaviors addressed in the first two brochures. The advice messages in our interventions are partly based on existing computer tailoring programs [54, 55] and partly formulated by the intervention developers (i.e. the authors of this paper). We felt that print-delivered materials would work best for our target group, as during the focus group interviews that we conducted, some of the participants stated that they did not use, or infrequently used the Internet, and that print-delivered materials would be easier to use. Furthermore, materials delivered to the recipients’ home may be more noticeable. Research has shown that printed material may be used and recognized better than Web-based or computer-delivered interventions [56, 57]. Internet- and print-delivered health-promoting materials have both been shown to be effective [58].

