#### Brochures one and two

The first two brochures each address one behavior (fruit consumption, vegetable consumption, snack consumption or PA) and its related determinants. The determinants addressed are *awareness of one’s own risk behavior*, *knowledge*, *attitude*, *self-efficacy*, *social influences*, *goal setting* and *action planning*.

An assessment tool is used to identify risk behaviors (i.e. not meeting the recommendations for the behaviors), accordingly, which two behaviors should be addressed in the brochures. The recipients can also choose two behaviors they would like to address. If they score unfavorably on more than two behaviors, their choice is taken into account. Moreover, the feedback addressing the behavioral determinants is tailored on the responses people have provided in the assessment tool.

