#### Design, participants and procedure

The two versions of the intervention will be evaluated in a randomized controlled trial with three study groups: traditional tailoring, EI-tailoring and a control group receiving generic, nontailored information. The primary outcome measures are fruit, vegetable and snack consumption, and PA. Mediating variables are awareness of one’s own behavior, attitude, self-efficacy, social support and intention towards more fruit, vegetable and snack consumption and PA. A process evaluation will be conducted at three-month follow-up, assessing the self-reported use, relevance and appreciation of the intervention.

It is hypothesized that both interventions are more effective than the control intervention and that the EI-tailoring intervention will reach higher effect sizes and higher acceptance among the target group than the traditional tailoring intervention. The required number of participants for this study is 1000, of which 500 should be of Dutch origin, 250 of Turkish origin and 250 of Moroccan origin. To be able to detect a small intervention effect (ES = 0.3), with a power of 0.8 and a significance level of p < .05, 250 people are needed in each study condition, which adds up to 750 participants in total. Taking a dropout rate of 10 % at each measurement moment into account, 1000 participants have to be included at baseline.

The target group consists of lower-educated adult women (lower vocational level or below), who are aged between 20 and 65 years, and who are of Dutch, Turkish or Moroccan origin. We use the standard definition for origin as described by Statistics Netherlands [68]. Participants with an insufficient knowledge of the Dutch language, or a health condition that may restrict their eating and/or PA behavior, are excluded from the study. Moreover, women whose baseline assessment shows that they do not perform the risk behaviors will be excluded from the study.

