#### Statistical analysis

Multivariable linear and logistic regression analysis will be conducted to assess group differences in the fruit, vegetable and snack intake and PA at different points in time. Moderation analysis will be conducted to assess whether the intervention effects are moderated by demographic factors, such as ethnic background or EI. Further, mediation analysis will be conducted to identify the factors that may explain the intervention effect (e.g. attitude and self-efficacy).

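### The sample size does not account for each woman being advised on only two of the four primary behaviours, and the stated analysis does not use the baseline selection

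*Protocol article*

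**What the plan says.** Under *Configuring intervention content and material*, the Protocol article says: "The recipient receives feedback on only two of the four behaviors". Under *Brochures one and two*, an assessment tool identifies each woman's risk behaviours, and her own preference settles the matter when there are too many: "If they score unfavorably on more than two behaviors, their choice is taken into account". *Brochure three* returns to the same two behaviours.

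Under *Design, participants and procedure*: "The primary outcome measures are fruit, vegetable and snack consumption, and PA". The same section sizes the trial once. It begins "To be able to detect a small intervention effect (ES = 0.3") and continues "with a power of 0.8 and a significance level of p < .05", with the result that "250 people are needed in each study condition, which adds up to 750 participants in total". The only inflation is for 10% loss "at each measurement moment into account, 1000 participants have to be included at baseline".

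Under *Statistical analysis*, linear and logistic regression will be used "to assess group differences in the fruit, vegetable and snack intake and PA at different points in time". No analysis set is named, and the two selected behaviours are not mentioned. The baseline measurement comes before stratification and random assignment.

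**The concern.** A woman in a tailored arm gets no tailored advice on two of the four outcomes on which her arm is judged. When arms are compared on one behaviour, the women not advised on it take part in the comparison but are expected to show little of the effect. The arm difference is then smaller than the effect in advised women, roughly in proportion to the share advised. The sample-size statement makes no allowance for this and does not say which of the two effects ES 0.3 describes.

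At stake is a null result on one or more primary outcomes for an intervention that works at the intended size on the behaviours it addresses. There is also a risk at the analysis stage. If the problem is noticed late, the tempting repair is to pick out women who received advice in the tailored arms only, and that would break the randomised comparison.

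**Working it through.** **Inputs from the article:** ES 0.3, power 0.8, significance level 0.05, 250 per condition, four primary outcomes, two behaviours advised per woman. **Assumed:** two-sided tests and a pairwise comparison of two arms. The article gives no share advised per behaviour, so a range is shown.

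**1. The plan's own figure.** Required n per arm = 2(1.960 + 0.842)² / 0.3² = 174.4, so 175 (176 with the t distribution). The stated 250 is not reproduced; it exceeds what the inputs need. At 250 per arm and a true arm difference of 0.3, 0.3 × √(250/2) = 3.354, and power = Φ(3.354 − 1.960) ≈ 92%. The smallest arm difference with 80% power at 250 per arm is 2.802 × √(2/250) = 0.251.

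The dropout step is consistent with the text: 750/0.9³ = 1029, or 750 × 1.1³ = 998, against the stated 1000.

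**2. The constraint on shares.** Let q be the share of women advised on a behaviour. With two behaviours per woman, the four values of q sum to at most 2, so their mean is at most 0.5.

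**3. Whole-group comparison, if ES 0.3 is the effect in advised women and there is no spill-over.** Arm difference = 0.3q; power at 250 per arm ≈ Φ(0.3q × √125 − 1.960), plus a negligible lower tail.

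| Share q | Arm difference | Power at 250 per arm |
|---|---|---|
| 0.3 | 0.09 | 17% |
| 0.4 | 0.12 | 27% |
| 0.5 | 0.15 | 39% |
| 0.6 | 0.18 | 52% |
| 0.7 | 0.21 | 65% |
| 0.8 | 0.24 | 77% |
| 0.9 | 0.27 | 86% |

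Power of 80% needs q ≥ 0.251/0.3 = 0.84. Three outcomes at 0.84 would need shares summing to 2.52, which exceeds 2. At most two outcomes can therefore reach 80%, and at least two must fall short, however the women choose.

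**4. Spill-over.** If unadvised women show a fraction s of the advised effect, then at q = 0.5 the arm difference is 0.3(0.5 + 0.5s). With s = 0.5 it is 0.225 and power is 71%. Reaching 80% needs s of about two thirds.

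**5. The other reading of ES 0.3.** If 0.3 is the whole-arm difference, power is about 92% (step 1). Without spill-over, advised women would then need 0.3/0.5 = 0.6 on average.

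**6. Comparison among selected women only.** At q = 0.5 this leaves 125 per arm. With ES 0.3, 0.3 × √(125/2) = 2.372 and power is about 66%. The effect detectable with 80% power is 2.802 × √(2/125) = 0.354 (0.356 with the t distribution). Power of 80% at ES 0.3 needs q ≥ 175/250 = 0.70, and since 3 × 0.70 = 2.10 exceeds 2, at most two outcomes can reach it.

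**The case against.** The strongest reply is that the article never says ES 0.3 is the effect in advised women. Read as the whole-arm difference, it gives power well above the target. This stands as a possible reading. It requires about 0.6 in advised women, which fits poorly with an effect that the article itself calls small.

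A second reply is that the article names no analysis set and that such detail is commonly left to a statistical analysis plan. A reader might infer that each behaviour will be tested in everyone; the text does not say so. The point does not depend on it, because restricting each outcome to selected women still leaves at least two outcomes below 80% at ES 0.3. The number recruited is fixed in this article, and a later analysis plan would not change it.

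A third reply is that zero spill-over is a worst case. The example messages for Dutch women offer fruit as a snack, so fruit advice could plausibly move the snack outcome. That is fair, and it is why the 39% is conditional. It would take about two thirds of the full effect in unadvised women to restore 80% at a 50% share.

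A fourth reply is that 50% is an average and need not describe any one behaviour. This also stands: a behaviour advised to 84% or more of women is protected. Finally, the whole-group comparison is a legitimate estimand, the effect of offering the programme, and should be kept.

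**Conclusion.** The concern holds in conditional form. The sample size takes no account of advice on two of four primary behaviours, and the stated analysis does not use the baseline selection. If ES 0.3 is the effect in advised women and spill-over is small, power at 250 per arm is about 39% at a 50% share, and at least two of the four primary outcomes miss 80%. The surplus of 250 over the roughly 176 per arm required does not close that gap.

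Two stronger readings are not supported. A reader might infer that the stated 80% power is simply not delivered; that depends on the meaning of ES 0.3 and on spill-over, and the article states neither. A reader might also infer that an effective intervention would most likely fail on most of the four outcomes. Even at 39% power on each, treated as independent, the chance that three or more fail is 0.61⁴ + 4 × 0.39 × 0.61³ ≈ 49%.

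**What to change.** 1. Run the two-behaviour selection on the baseline questionnaire, including the woman's own choice, for every woman, control arm included. Store the result before randomisation.
2. For each behaviour, pre-specify an analysis of all randomised women, in all three arms, for whom that behaviour was selected. The selection precedes randomisation and is made identically in every arm, so the randomised comparison is preserved.
3. Report the whole-group comparison alongside it.
4. State whether ES 0.3 is the effect in advised women or the whole-arm difference.
5. Give the expected share selected per behaviour and restate power on those numbers. At a 50% share, about 125 per arm, this is 66% at ES 0.3, or 80% at about ES 0.36.

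The cost is one stored variable, derived from the baseline assessment, and some analysis wording. The drawback is that the stated per-behaviour power becomes less favourable. Restriction alone does not bring every outcome to 80%: at a 50% share, that would take 175/0.5 = 350 per arm analysed, or about 1050/0.9³ ≈ 1440 recruited. A composite of each woman's two selected behaviours is optional, because it answers a different question from the four behaviour-specific outcomes.
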